#### Functional connectivity analysis of the attentional network

The degree of signal synchronization in the time domain during the initial 6-min resting phase was assessed using Pearson correlation analysis across all measured brain regions. This analysis provided a connectivity matrix that captured both intra- and interhemispheric connectivity relationships. The elements within the matrix represented the correlation coefficients of the paired channels, with rows and columns corresponding to the channel numbers.Graph Theoretical Analysis was subsequently employed to calculate various node metrics. Nodes with a sparsity greater than 20% were selected for analysis to assess the overall characteristics of the brain network organization. The analysis was conducted using the Graph Theoretical Network Analysis (GRETNA) toolbox. The metrics calculated included global efficiency (reflecting network efficiency), local efficiency (reflecting local network efficiency), and the small-world network property. Higher values of these metrics indicate higher network efficiency and adherence to a small-world network structure.

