### fNIRS data collection

To investigate the potential mechanisms of Baduanjin training on post-stroke cognitive dysfunction, this study will collect functional near-infrared spectroscopy (fNIRS) data from participants both before and after 12 weeks of intervention. The equipment utilized for this purpose is the Wuhan Zilian Hongkang model BS-3000 fNIRS equipment.Prior to data collection, the study's objectives were thoroughly explained to the participants. They were instructed to keep their heads at rest during the tests and minimize swallowing movements to minimize potential testing errors. The areas sampled include the premotor cortex (PMC), supplementary motor area (SMA), primary motor cortex (M1), and sensorimotor cortex (SMC).The 37-channel fiber optic cap employed in this study comprises 12 light sources and 12 detectors, spaced 3 cm apart in a rectangular grid of 3 rows by 8 columns. Light is emitted from a source and penetrates the scalp and skull, where it is absorbed by oxyhemoglobin and deoxyhemoglobin in the cortex. The remaining light is then detected. Changes in hemoglobin concentration within the region traversed by the channel serve as indicators of local neuronal activity.

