### fNIRS data analysis methods

#### Pre-processing

The data processing steps for functional near-infrared spectroscopy (fNIRS) were as follows:

①The fNIRS data was initially converted from NIRS format to MAT format.②Wavelet-MDL (Minimum Description Length) was employed to remove noise from sources such as heartbeat and breathing.③An HRF (Hemodynamic Response Function) low-pass filter was applied to eliminate signal drift and artifacts.④The necessary parameters for the General Linear Model (GLM) were selected, and β-values were estimated for the model using a t-test with a significance threshold of *P* < 0.05.To account for multiple comparisons, the False Discovery Rate (FDR) correction was utilized. This correction method was employed to output statistical information, including T-values, activation regions, and statistical threshold values.

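### One reading for all three graph metrics is unsafe: at a fixed edge density, a rise in global efficiency alone can mean a loss of small-world structure

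*Protocol article*

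**What the plan says.** All of this is in the protocol article.

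- **Edges.** In the section on functional connectivity analysis of the attentional network, signal synchronisation "during the initial 6-min resting phase was assessed using Pearson correlation analysis across all measured brain regions".
- **Threshold.** In the same section: "Nodes with a sparsity greater than 20% were selected for analysis".
- **Metrics.** "The metrics calculated included global efficiency (reflecting network efficiency), local efficiency (reflecting local network efficiency), and the small-world network property".
- **Reading.** One sentence covers all of them: "Higher values of these metrics indicate higher network efficiency and adherence to a small-world network structure".
- **Layout.** Under fNIRS data collection: "The 37-channel fiber optic cap employed in this study comprises 12 light sources and 12 detectors". The optodes form a 3 x 8 grid with 3 cm between neighbours.
- **Noise.** Participants are "instructed to keep their heads at rest during the tests and minimize swallowing movements". Under Pre-processing, a wavelet method "was employed to remove noise from sources such as heartbeat and breathing", followed by a low-pass filter.

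The connectivity analysis serves a declared aim (Introduction, and the Discussion part of the Abstract). It is not among the listed primary or secondary outcomes.

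**The concern.** The quoted sentence attaches two meanings, more efficient and more small-world, to a higher value of any of the three metrics. Small-world structure means high local clustering together with short paths. Global efficiency measures only the short paths. When the number of edges is fixed, replacing local links by random long-range links shortens paths and breaks up clusters. Global efficiency then rises while local efficiency, clustering and the small-world index can fall. The stated rule would read that rise as closer adherence to small-world structure when the opposite has happened.

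At stake is the mechanistic conclusion. This is the only stated rule that turns the connectivity metrics into a statement about brain networks. Recording noise can also move the metrics while the network stays the same, and the rule gives no means of telling the two apart.

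**Working it through.** **1. The plan's own figure.** Neighbouring source-detector pairs on a 3 x 8 grid: 3 x 7 + 2 x 8 = 21 + 16 = 37. This reproduces the stated 37 channels. There are 37 x 36 / 2 = 666 channel pairs, so 20% density keeps about 0.20 x 666 = 133 edges.

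**2. Definitions.**

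- Global efficiency Eg = mean over node pairs of 1/d, where d is the shortest path length.
- Local efficiency El = mean over nodes of the global efficiency of the subgraph formed by that node's neighbours.
- Small-world index sigma = (C / C_random) / (Eg_random / Eg), where C is clustering, the random values come from degree-preserving rewired graphs, and the efficiency ratio stands in for the path-length ratio.

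**3. Simulation.** From the document: 37 channels, the grid, Pearson correlation, 6 minutes at rest, 20% sparsity (30% was also tried). Assumed, because the document does not give them:

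- sparsity means a fixed edge density;
- about 72 effective samples (2 x 0.1 Hz x 360 s = 72, with an assumed 0.1 Hz low-pass);
- two signal structures: spatial (correlation decaying with distance, plus mirror-channel correlation) and modular;
- noise SD of 0, 0.5, 1 or 2 times signal SD.

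There were 60 runs per cell, 12 for sigma. The signal covariance was the same at every noise level. No denoising step was modelled.

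**4. Channel-independent noise, fixed density.**

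| Structure, density | Metric | Noise 0 | 0.5 | 1 | 2 |
|---|---|---|---|---|---|
| Spatial, 20% | Eg | 0.512 | 0.519 | 0.535 | 0.555 |
| | El | 0.704 | 0.664 | 0.579 | 0.474 |
| | sigma | 2.19 | 1.94 | 1.57 | 1.34 |
| Spatial, 30% | Eg | 0.613 | 0.619 | 0.629 | 0.639 |
| | El | 0.774 | 0.760 | 0.715 | 0.652 |
| | sigma | 1.66 | 1.58 | 1.28 | 1.16 |
| Modular, 20% | Eg | 0.225 | 0.293 | 0.512 | 0.555 |
| | El | 0.919 | 0.885 | 0.686 | 0.466 |
| | sigma | 1.86 | 2.09 | 2.28 | 1.44 |
| Modular, 30% | Eg | 0.574 | 0.598 | 0.624 | 0.640 |
| | El | 0.887 | 0.860 | 0.756 | 0.656 |
| | sigma | 2.31 | 2.28 | 1.68 | 1.22 |

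Eg rises and El falls in all four cells. Sigma falls throughout in three; in the modular structure at 20% it rises before it falls. So a rise in Eg can accompany a loss of small-world structure, but need not. In the first cell, the change from noise 0 to 2 is +0.043 for Eg (8%), -0.230 for El (33%) and -0.85 for sigma (39%). A second run on the same layout at 20% gave the same signs: Eg 0.515 to 0.553, El 0.643 to 0.467, clustering 0.488 to 0.308.

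**5. Other kinds of noise, 20% density, noise 0 to 2** (in the bad channels the noise SD was doubled).

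| Noise | Spatial Eg | Spatial El | Spatial sigma | Modular Eg | Modular El |
|---|---|---|---|---|---|
| Seven bad channels | 0.511 to 0.409 | 0.696 to 0.620 | 2.21 to 1.66 | 0.223 to 0.408 | 0.908 to 0.732 |
| Shared across channels | 0.511 to 0.419 | 0.700 to 0.631 | 2.18 to 1.27 | 0.224 to 0.420 | 0.919 to 0.727 |
| Spatially smooth | 0.511 to 0.487 | 0.699 to 0.777 | 2.12 to 2.53 | 0.223 to 0.489 | 0.924 to 0.775 |

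In the spatial structure, smooth noise reverses both directions seen in step 4, and shared noise lowers Eg. In the modular structure, all three raise Eg and lower El. The sign therefore depends on the kind of noise and on the underlying network.

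**The case against.** **The sentence can be read metric by metric.** On that reading the two efficiencies index efficiency, the small-world property indexes small-world structure, and the sentence is true by definition. That is possible, but it is not what the sentence plainly says: it gives both meanings to all the metrics together. If the metric-by-metric reading is meant, saying so costs one line.

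**Fixed density is inferred.** The criterion is worded as applying to nodes, not edges. With an absolute threshold of r > 0.3, channel-independent noise lowers both metrics (spatial structure: Eg 0.751 to 0.052, El 0.847 to 0.033), and the opposite movement disappears. This stands as a condition on the point. It does not rescue the rule: with the same threshold, shared noise raises both (Eg 0.738 to 0.998, El 0.837 to 0.999), because nearly every pair becomes an edge.

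**The small-world property is already calculated, and some noise is removed.** Both are true. The sentence still invites a small-world reading of global efficiency. How channels or segments are screened is detail that an article may leave to the full protocol, and its absence is not held against the plan.

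**A stronger reading is tempting:** that noisier recordings in general raise global efficiency and lower local efficiency, so that Baduanjin patients who sit more quietly at week 12 would be read as declining. The documents do not support it. They report no noise difference between arms; the keep-still instruction is given without distinction by group; there is a concurrent control arm; and technicians and analysts are to be blinded. Better attention after training might reduce movement, but neither the size nor the kind of such a noise change is given. Step 5 shows that the kind of noise can reverse the sign. Any false-positive rate for that scenario would only restate an assumed difference.

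**Conclusion.** The point holds in a limited form. If the sparsity criterion fixes edge density, a higher global efficiency taken alone does not show adherence to small-world structure and can accompany its loss. In the spatial structure at 20% density, global efficiency rose by 0.043 while the small-world index fell from 2.19 to 1.34. The signs carry the argument. The sizes rest on the assumed sample count, signal structures and noise levels, the largest of which is four times the signal variance.

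Noise can move these metrics with no network change, but no single direction can be claimed and no bias between arms is shown. Severity is minor: no listed outcome, sample size or significance level depends on these measures. The mechanistic conclusion does.

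**What to change.** - Replace the blanket sentence with a separate reading for each metric, and say whether the 20% criterion is an edge density.
- Infer small-world structure only from clustering and path length, each normalised to degree-matched random networks from the same recording, and from their ratio.
- Do not call a change in global or local efficiency alone a network improvement or decline. Interpret it together with the other metric and the normalised index.
- Tabulate signal quality by arm and visit. This is needed because the normalised index is not immune to noise either: spatially smooth noise raised it from 2.12 to 2.53 in the spatial structure.

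The cost is a few lines of text and slightly more analysis of data already planned. The downside is that an isolated rise in one metric no longer counts as benefit.

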### Safety measurements

The assessment of safety in this study focused on monitoring the incidence and severity of adverse events. Any adverse events occurring during the study were diligently documented in the Adverse Event Record Sheet, which included details such as symptoms, onset time, duration, and any treatment measures administered.Adverse events were categorized into three levels based on severity:general adverse events,significant adverse events and serious adverse events.For serious adverse events, a dedicated report form was completed. Safety evaluation was conducted by synthesizing all relevant factors. The evaluation parameters included:Level 1: Safe, without any adverse reactions;Level 2: Relatively safe, with mild adverse reactions that did not require treatment, allowing for continued training;Level 3: Safety concerns, with a moderate degree of adverse reactions that could continue with treatment;Level 4: Due to serious adverse reactions, discontinuation of the study was necessary.Depending on the circumstances, safety assessments were performed for subjects at the conclusion of the intervention to ensure their well-being throughout the trial.

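### Serious adverse events are classed by severity rather than by outcome, so they may be under- or over-counted

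*Protocol article*

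**What the plan says.** All of the relevant text is in the protocol article under Safety measurements.

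- **Focus of the safety assessment:** "The assessment of safety in this study focused on monitoring the incidence and severity of adverse events". Seriousness is not named as a separate attribute.
- **Classification:** "Adverse events were categorized into three levels based on severity". The levels are general, significant and serious, in that order.
- **Consequence of the top class:** "For serious adverse events, a dedicated report form was completed".
- **Recording of events in general:** "Any adverse events occurring during the study were diligently documented in the Adverse Event Record Sheet". The details given as examples are symptoms, onset time, duration and treatment given.
- **Separate four-level safety rating:** it runs from no reaction, through mild, to "Level 3: Safety concerns, with a moderate degree of adverse reactions that could continue with treatment" and then "Level 4: Due to serious adverse reactions, discontinuation of the study was necessary".

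The article gives no boundaries between the three event classes and no outcome-based criterion for calling an event serious.

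**The concern.** Severity is the intensity of an event. Seriousness is what the event led to, such as death, threat to life, admission or a prolonged stay, or lasting disability. The two often go together but need not. A fall injury or a brief recurrent vascular event can be moderate in intensity and still lead to admission. An intense headache can resolve without consequence.

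The article makes serious the last step of a scale whose stated basis is severity, and attaches the dedicated form to that step. If site staff apply the rule as written, the set of events called serious is not the set that is serious by outcome.

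This matters more than usual here. Participants are within one year of a first stroke and are assigned a movement programme of 40 minutes, five times a week for 12 weeks. The Discussion already describes the intervention as safe. With small groups, a few misclassified events could change how the safety result reads.

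**Working it through.** The article states no serious-event count or rate, so there is no figure to reproduce. The check is a reading of the text, followed by a statement of what can and cannot be sized.

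**Step 1. Basis and consequence.** The three-class sentence names severity as the basis and lists serious last. The dedicated form is then completed for serious events. Taken together, the form follows from a severity class. The text does not say that the form is confined to that class, but no other trigger is given.

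**Step 2. How the word is used elsewhere in the section.** In the four-level rating, serious reactions come after mild and moderate ones, the position where severe would normally stand. The opening sentence speaks of incidence and severity. Three places in one section therefore treat the concept as a matter of degree.

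**Step 3. Search for another definition.** No other section of the article gives an outcome-based criterion for a serious adverse event. The exclusion criteria use the word for concurrent disease, which is a different matter. The statistical analysis section specifies no safety comparison.

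**Step 4. Cross-classification.** Set the stated rule (top severity class) against an outcome-based rule:

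| | Serious by outcome | Not serious by outcome |
|---|---|---|
| Top severity class | both rules agree | called serious (over-count, *o* events) |
| Lower severity class | not called serious (under-count, *u* events) | both rules agree |

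The net error in the serious-event count is *o* − *u*. It can be positive, negative or zero, and it can be zero while individual events are still misclassified. The article gives neither *o* nor *u*, nor any event rate from which to derive them.

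**Step 5. Can the record sheet repair it later?** Every event goes on the Adverse Event Record Sheet, so a misclassified event is still on file. The fields named there do not include outcome or admission. The list is given by way of example, so such a field may exist, but later reclassification cannot be relied on from what is stated.

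**Step 6. Scale only.** The sample size section plans 24 participants per group. One reclassified participant changes a group's proportion with a serious event by 1/24 = 4.2 percentage points, and two change it by 2/24 = 8.3. These figures show how coarse the scale is. They are not an estimate of how often misclassification would occur.

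**The case against.** The strongest reply is that the class boundaries are simply not given. A journal article commonly leaves such criteria to the full protocol or to the report form itself. If either defines serious by outcome, a moderate event leading to admission would be handled correctly. The labels general and significant are not plain intensity grades, and the article's English is loose in other places: Baduanjin is also rendered as octogenarian training and as octopus training. Severity may therefore stand for importance. Finally, adverse events are not among the primary or secondary outcomes, and the article promises no count of serious events by arm.

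Much of this stands. A reader might infer that moderate events with serious outcomes will not be reported as serious, that the serious-event count is wrong, or that it is too low. The article supports none of these. Without boundaries the count *may* be wrong, and the error can go either way. A reader might also infer that such events go unreported to those overseeing safety. The text does not support that either, because every event is recorded and no reporting line attached to the dedicated form is described.

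One part does not stand. The point is not that a definition is missing but that a basis is stated, and it is the wrong one. If the full protocol uses outcome criteria, the published sentence contradicts it and still needs correcting. Loose translation is possible, but the four-level rating also uses serious as the grade above moderate, so the text gives no positive support for the outcome reading.

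**Conclusion.** The point holds in a limited form. As written, the safety section merges intensity and seriousness, and completes the dedicated form on the strength of a severity class. Serious events may be under- or over-counted, and the document does not allow the amount or the direction to be determined.

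This rests on two assumptions: that staff apply the classification as the article words it, and that no undisclosed definition overrides it. If an outcome-based definition is already in use, the defect is confined to the published wording. No efficacy endpoint, sample size or test is affected. The correction is worth making because the rule governs which events receive serious-event documentation.

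**What to change.** In Safety measurements, replace the single three-class scale with two fields recorded for every adverse event:

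1. **Severity:** mild, moderate or severe.
2. **Seriousness:** yes or no, judged by listed outcome criteria such as death, threat to life, admission or prolonged stay, or lasting disability.

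State that the dedicated form is completed whenever seriousness is yes, whatever the severity. Tabulate both fields by arm. If the full protocol already defines serious events by outcome, bring the article's wording into line with it.

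The cost is one extra field on the Adverse Event Record Sheet, a change of wording, and possibly a few more forms. The change concerns classification and documentation only. It leaves the four-level rating's provisions on continuing or stopping as they are.

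### The four-level safety rating leaves some outcomes without a level, shifts from adverse events to adverse reactions, and sits beside an end-of-intervention safety assessment that is only conditional

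*Protocol article*

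**What the plan says.** All of the relevant text is in the Safety measurements section of the protocol article.

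- Purpose: "The assessment of safety in this study focused on monitoring the incidence and severity of adverse events".
- Recording: "Any adverse events occurring during the study were diligently documented in the Adverse Event Record Sheet". No arm is excluded, and a serious event also gets its own report form.
- First scheme, for events: "Adverse events were categorized into three levels based on severity:general adverse events,significant adverse events and serious adverse events".
- Second scheme, an overall evaluation: "Safety evaluation was conducted by synthesizing all relevant factors". It has four levels. The lowest is "Level 1: Safe, without any adverse reactions". Next come "Level 2: Relatively safe, with mild adverse reactions that did not require treatment, allowing for continued training" and "Level 3: Safety concerns, with a moderate degree of adverse reactions that could continue with treatment". Level 4 is for serious reactions that made discontinuation of the study necessary.
- Timing: "Depending on the circumstances, safety assessments were performed for subjects at the conclusion of the intervention".

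Elsewhere, the section on randomization, allocation concealment and blinding says that researchers, participants and coaches cannot be blinded. The Assessment of results section promises blinded assessors for the primary and secondary outcomes. Safety is not listed among either.

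**The concern.** The section collects one thing, adverse events in three classes, and then judges safety on another, adverse reactions in four levels, without connecting the two. A rater with a completed record sheet cannot always derive the level from it. Two raters could place the same course of events in different levels, or in none.

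The lowest level carries the label Safe, which is the word most likely to be carried into a results paper. If the share of participants at that level were compared between arms, the result would depend on how raters filled the gaps, on what they took a reaction to be, and on who was assessed at the end of the intervention. With allocation known to researchers and coaches, each of these is a route by which knowledge of the arm could enter the safety result.

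**Working it through.** The article gives no adverse event frequencies and no safety sample size, so there is no figure to reproduce. The check is whether the levels, read as printed, cover the possible outcomes.

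**1. Coverage of the levels.** The wording of Levels 2 to 4 uses three features: severity (mild, moderate, serious), whether treatment was needed (yes, no), and whether the participant continued (yes, no). That gives 3 × 2 × 2 = 12 combinations for a participant with a reaction. Level 4's discontinuation is taken here to be the participant's.

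| Severity | Treated, continues | Treated, stops | Untreated, continues | Untreated, stops |
|---|---|---|---|---|
| Mild | none | none | Level 2 | none |
| Moderate | Level 3 | none | none* | none |
| Serious | none | Level 4 | none | Level 4 |

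Covered: 1 + 1 + 2 = 4. Without a level: 12 − 4 = 8.

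*Level 3 is ambiguous. The table reads it as continuing while the reaction is treated. If it means continuing the study treatment, the starred cell also becomes Level 3, so 5 are covered and 12 − 5 = 7 are not. On both readings, a mild reaction that needed treatment and a serious reaction without discontinuation have no level.

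**2. Events against reactions.** The purpose, the recording rule and the three classes are all stated for adverse events. All four levels are stated for adverse reactions. There are two ways to read this:

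- If the words are interchangeable, any recorded event rules out Level 1, and only the gaps in step 1 remain.
- If a reaction is an event related to the intervention, a participant with an unrelated adverse event has no reaction and could be rated Level 1.

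The printed text does not decide between them, and the rating differs according to which is used.

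**3. Three classes against four levels.** The classes are general, significant and serious. The levels grade reactions as none, mild, moderate and serious, with further conditions attached. Only the word serious is common to both. No rule says whether a general event is mild, or whether a significant one is moderate. The three classes are also said to rest on severity, yet the top one is seriousness, which is a different attribute.

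**4. Who is assessed.** Event recording is unconditional. The safety assessment at the end of the intervention is qualified by circumstances that are not stated. The Study design and Assessment of results sections already place outcome assessments at week 12, so there is no logistical reason for the safety assessment to be selective.

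**The case against.** The strongest reply is that the underlying data are sound. All events during the study are recorded with symptoms, onset, duration and treatment, without restriction by arm, and none leaves the dataset. The statistical analysis section provides frequencies, percentages and a chi-square test for counts, so incidence can be compared between arms. The four-level rating is not listed as an outcome. This is also a condensed article, and definitions or a causality assessment may sit in the full protocol or on the record form. All of that stands, and the absence of a causality procedure is not held against the article here. What it does not answer is that the scale is printed level by level and has gaps as printed.

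Several stronger readings are tempting, and the text does not support them:

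- A reader might infer that a participant with a serious event such as a recurrent stroke will be rated Safe. That needs a causality filter which the article never describes; reaction and event may simply be used as synonyms.
- A reader might infer that Level 2, because it mentions training, cannot apply to the 24 controls among 72 participants. Only Level 2 uses that word, controls receive rehabilitation sessions, and the Introduction and the participation scale use training for rehabilitation in general.
- A reader might infer that unblinded staff choose whom to rate. The article names no safety rater, and the conditional phrase attaches to the end-of-intervention assessment, not clearly to the four-level rating.
- A reader might infer that the gaps affect common events. Without frequencies, only the gaps themselves can be shown.
- The Discussion already describes Baduanjin as safe, but that is a general remark and not a planned conclusion from this scale.

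**Conclusion.** The point holds in a limited form. The rating is not exhaustive: 8 of 12 combinations of severity, treatment and continuation have no level, or 7 of 12 on the wider reading of Level 3. These counts describe the wording. They are not a proportion of patients, and the documents do not allow one to be estimated. The rating uses a different term from the one that defines safety, and it is not tied to the three event classes. The end-of-intervention safety assessment is conditional in a trial with unblinded researchers and coaches.

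A between-arm comparison of this rating would therefore be unreliable. That a participant could be rated Safe after an adverse event follows only on the assumption that a reaction means a related event. Safety as such can still be compared, through counts of recorded events, and the primary outcomes are not affected.

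**What to change.** In the Safety measurements section:

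- Carry out the end-of-intervention safety assessment for every participant in all groups, at the week 12 visit already planned.
- Record severity, seriousness and relation to the intervention as three separate items for each event.
- Make the main safety comparison the number of patients per arm with any adverse event and the number with any serious adverse event, whatever the judged relation.
- Keep the four-level rating only as a supplement.

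The sponsor should also reconcile reaction with event, the four levels with the three classes, and whether discontinuation of the study in Level 4 refers to the participant or to the trial. This concerns recording and reporting only; no treatment or stopping rule is proposed.

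The cost is a minor change to the record sheet and the section wording, with no extra visit. Event counts reported in this way may look less favourable than the rating would.
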